[figure not shown][figure not shown][figure not shown]

## 1. INTRODUCTION / REVIEW:

Both sepsis and septic shock represent a major growing global burden and a challenge for physicians because of their increasing incidence and great pathophysiological, molecular, genetic, and clinical complexity. The incidence of sepsis and septic shock has continuously increased since the first consensus definition (Sepsis-1) in 1991, reaching around 49 million cases of sepsis and 11 million sepsis-related deaths worldwide in 2017 **(Chiu and Legrand 2021)**

Severe sepsis is defined as sepsis associated with organ dysfunction, hypoperfusion, or hypotension. Perfusion abnormalities may include, but are not limited to, lactic acidosis, oliguria, or alteration in mental status. In 2016, the surviving sepsis campaign defined sepsis as a life-threatening organ dysfunction caused by a dysregulated host response to infection **(Singer et al., 2016)**.

In septic patients, TNF- $\alpha$  is the first pro-inflammatory cytokine that is released, followed by IL-1, IL-6, and IL-8. TNF- $\alpha$  and IL-1 are the most important proinflammatory cytokines; they are biologically closely related, act synergistically, and are largely responsible for the clinical manifestation of sepsis **(Schulte et al., 2013)**. Fluoxetine is an antidepressant that belongs to a group of medicines called serotonin selective reuptake inhibitors (SSRIs). It works by increasing the amount of a natural chemical called serotonin in the brain **(Roumestan et al., 2007)**.

It is now recognized that SSRIs also have a wide range of peripheral effects including regulation of immune and metabolic **processes (Olguner Eker et al., 2017; Szałach et al., 2019)**. Furthermore, SSRIs have been shown to protect against sepsis in animal models **(Rosen et al., 2019)** and improve outcomes in patients infected with SARS-CoV-2 **(Reis et al., 2022)**. The mechanisms underlying these protective effects are unclear. SSRIs have been reported to have anti-inflammatory effects, which suggests they may protect against overwhelming inflammatory responses and cytokine storm **(Durairaj et al., 2015; Tynan et al., 2012)**. They have also been reported to regulate aspects of systemic metabolism that are dysregulated during sepsis and other inflammatory states including lipid metabolism **(Chiu et al., 2021; Pan et al., 2018; Rozenblit-Susan et al., 2016)**.

[figure not shown][figure not shown][figure not shown]

## 2. AIM OF THE STUDY:

The aim of this study is to evaluate the efficiency of fluoxetine as an adjuvant therapy in the treatment of severe sepsis and its effect on multiple organ dysfunction and mortality in septic patients.

## 3. METHODS:

**Ethical Considerations:** The study will be conducted after taking approval from the Research Ethics Committee at Ain-Shams University Hospital, Cairo, Egypt. An informed written consent will be obtained from each participant's legal guardian. Confidentiality of the data will be preserved.

**Study Design:** Randomized, controlled, double-blind study.

**Study Setting and Duration:** This study will be carried out at the Anesthesiology Department of Ain-Shams University Hospital, Cairo, Egypt from December 2024 to June 2025.

## Patients and Methods:

### Study Population:

- ASA II, III 60 patients, aged 18-65 years, BMI 30-35, admitted to ICU and diagnosed as patients with severe sepsis.
- The diagnosis of severe sepsis was established according to the definitions of the Surviving Sepsis Campaign (SSC) (**Singer et al., 2016**).

**Severe sepsis definition = sepsis-induced tissue hypoperfusion or organ dysfunction (any of the following thought to be due to the infection)**

Sepsis-induced hypotension

Lactate above upper limits laboratory normal

Urine output  $< 0.5 \text{ mL/kg/hr}$  for more than 2 hrs despite adequate fluid resuscitation

Acute lung injury with  $\text{Pao}_2/\text{Fio}_2 < 250$  in the absence of pneumonia as infection source

Acute lung injury with  $\text{Pao}_2/\text{Fio}_2 < 200$  in the presence of pneumonia as infection source

Creatinine  $> 2.0 \text{ mg/dL}$  ( $176.8 \text{ }\mu\text{mol/L}$ )

Bilirubin  $> 2 \text{ mg/dL}$  ( $34.2 \text{ }\mu\text{mol/L}$ )

Platelet count  $< 100,000 \text{ }\mu\text{L}$

Coagulopathy (international normalized ratio  $> 1.5$ )

## Exclusion Criteria:

- Patients with Late septic shock at presentation with multiple organ failure
- APACHE II score on admission >25
- Preexisting liver cirrhosis
- patients with prolonged QT interval or premature ventricular beats
- Preexisting end-stage renal disease
- Pregnancy
- History of allergy to fluoxetine
- Patients with malignancies
- Uncontrolled hemorrhage
- Burns
- Previous steroid therapy
- Death within 24 hours of ICU admission
- Concurrent use of MAO inhibitors or linezolid or any drugs increase QR interval like flecainide
- History of seizures
- Age more than 65 years

Patients will be recruited after admission to the Ain Shams University Hospital. Randomization will be performed using computer-generated random number tables in opaque sealed envelopes prepared by an anesthesiologist who will not participate in the study. Patients will be randomly divided into two groups using a computer-generated random number chart:

- **Group 1:** Receiving conventional sepsis therapy alone according to our hospital protocol (summarized as the following): -
- Initial Resuscitation:

- Patients with sepsis-induced tissue hypoperfusion with suspicion of hypovolemia to achieve a minimum of 30 mL/kg of crystalloids.
- The goals of initial resuscitation of sepsis-induced hypoperfusion included all of the following:
  - MAP  $\geq$  65 mm Hg.
  - Urine output  $\geq$  0.5 ml/kg/hr.
  - CVP 8–12 mm Hg.
  - Central venous oxygen saturation (ScvO2) 70%.
- Diagnosis
- Cultures including blood cultures before antimicrobial therapy if no delay in the start of antimicrobial.
- Antimicrobial therapy
- Iv broad spectrum (one or more anti-infective drug) to cover all likely pathogen according to site of infection and hospital antibiogram.
- Source control
- Source of sepsis should be identified, and intervention should be taken as soon as possible to control it (e.g. surgical drainage and change of infected lines)
- Vasopressor
- If adequate fluid resuscitation therapy was not able to restore hemodynamic, Vasopressor therapy initiated to target a mean arterial pressure (MAP) of 65 mm Hg.
- Norepinephrine as the first-choice vasopressor, epinephrine added to and potentially substituted for norepinephrine when an additional agent is needed to maintain adequate blood pressure
- Corticosteroids
- If adequate fluid resuscitation and vasopressor therapy are not able to restore hemodynamic stability, IV hydrocortisone at a dose of 200 mg/day.

- **Group 2:** Receiving conventional sepsis therapy in addition to fluoxetine 40 mg ( Prozac 20mg , Elli Lillys medical company Indianapolis, Indiana, United States) ® (1) daily for 28 days or until discharge from the ICU or death.
- **Primary outcome:** vasopressor dose.
- **Secondary outcome:** ICU Mortality & Organ dysfunction.

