### **Clinical Data:**

- To be evaluated up to a maximum follow-up period of 28 days of ICU stay:
  - Length of hospital stay
  - Need for and duration of mechanical ventilation
  - Need for and duration of vasopressor and inotropic support
  - Need for hemodialysis
  - Final outcome:
    - Survivors:
      - A) Patients recovered and discharged from ICU.
      - B) Patients still morbid and stayed in ICU more than 28 days.
    - Non-survivors:
      - Death before the completion of the 28 days of study period.

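### Excluding deaths in the first 24 hours of ICU stay lets randomised patients be removed because of an outcome, and conflicts with the protocol's own definition of non-survivors

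*Protocol*

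**What the plan says.** The Protocol's Exclusion Criteria list includes "Death within 24 hours of ICU admission". Other items in the same list are judged at presentation or at admission, for example "APACHE II score on admission >25".

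The paragraph after the list gives the only statement on timing: "Patients will be recruited after admission to the Ain Shams University Hospital". It fixes no hour for randomisation or first dose relative to ICU admission. Fluoxetine is then given "daily for 28 days or until discharge from the ICU or death".

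The secondary outcome is "ICU Mortality & Organ dysfunction". The Clinical Data section, with data "To be evaluated up to a maximum follow-up period of 28 days of ICU stay", defines non-survivors as "Death before the completion of the 28 days of study period". It makes no exception for the first 24 hours.

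**The concern.** An exclusion criterion should be a fact that is known before allocation. Death within 24 hours is an event in the future for anyone enrolled during those 24 hours, so for such a patient the criterion can be applied only after randomisation, and only because the patient died. Removing patients on the basis of an outcome means that the groups compared are no longer the groups that were randomised.

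Mortality is a named secondary outcome and part of the stated aim, so the rule acts directly on a result that the trial will report. It also acts on vasopressor dose (the primary outcome in the outcome list) and on SOFA (the primary outcome in the first sample-size paragraph), because patients who die early are likely to be among the sickest and would leave those data too.

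**Working it through.** **Step 1: the texts side by side.** Take a randomised patient who dies 20 hours after ICU admission.

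- Under Exclusion Criteria, the patient is excluded.
- Under Clinical Data, the patient is a non-survivor, having died before 28 days were complete.

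Both rules cannot be followed for this patient.

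**Step 2: can such a patient exist?** Only if randomisation can fall within 24 hours of ICU admission. The protocol does not rule this out. Recruitment follows hospital admission, APACHE II is taken on admission, late septic shock is judged at presentation, and the background care common to both groups begins with initial resuscitation and with cultures before antimicrobials. These point to early enrolment, but they do not state it.

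**Step 3: how far could the mortality comparison move?** The protocol states no mortality rate and no early-death rate, so there is no figure of its own to reproduce. The inputs are:

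- 60 patients ("ASA II, III 60 patients, aged 18-65 years"). Equal allocation is assumed, giving 30 per arm.
- Equal true mortality of 9/30 = 30.0% per arm (assumed), with 12/30 = 40.0% as a second case.
- The number of early deaths removed per arm (assumed, varied below).

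Formula: observed mortality in an arm = (deaths - removed) / (30 - removed). Difference = fluoxetine minus control. The true difference is 0 in every row.

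| True deaths per arm | Removed, fluoxetine v control | Fluoxetine | Control | Difference (points) |
|---|---|---|---|---|
| 9/30 | 3 v 1 | 6/27 = 22.2% | 8/29 = 27.6% | -5.4 |
| 9/30 | 3 v 0 | 6/27 = 22.2% | 9/30 = 30.0% | -7.8 |
| 9/30 | 1 v 3 | 8/29 = 27.6% | 6/27 = 22.2% | +5.4 |
| 9/30 | 2 v 2 | 7/28 = 25.0% | 7/28 = 25.0% | 0 |
| 12/30 | 3 v 1 | 9/27 = 33.3% | 11/29 = 37.9% | -4.6 |
| 12/30 | 3 v 0 | 9/27 = 33.3% | 12/30 = 40.0% | -6.7 |

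The sign depends on which arm loses more early deaths. Equal removal leaves the difference alone but understates mortality in both arms.

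**Step 4: scale.** The standard error of 6/27 v 8/29 is √(0.222×0.778/27 + 0.276×0.724/29) = √(0.00640 + 0.00689) ≈ 0.115, or 11.5 points. A shift of 5.4 points is therefore about half a standard error.

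**The case against.** The strongest objection is about timing. The protocol never says when randomisation takes place. The population is described as already in the ICU and already diagnosed. If every patient were randomised at least 24 hours after ICU admission, the criterion would be settled beforehand and would remove nobody who had been randomised. This stands. A reader might infer that the criterion can only ever operate after randomisation, but the document supports only the conditional statement that it would do so for patients randomised within the window, and that nothing prevents this.

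A reader might also infer that early deaths on fluoxetine would vanish from the safety data. No section says so. For mortality, the Clinical Data definition points the other way, and analysis sets may be defined in a statistical analysis plan that is not at hand. What the protocol contains is an unreconciled conflict, not a stated instruction to discard deaths.

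Nor is the 5.4-point figure an estimate of bias. It is one chosen scenario, and others give the opposite sign or zero. The rule is worded the same for both arms, so it produces a systematic error only if treatment alters very early death or if the rule is applied differently by arm. Otherwise an uneven split is chance. Daily dosing makes exposure within the window short, and excluding high APACHE II scores and late septic shock with multiple organ failure should make early deaths fewer. Mortality is also secondary and has no power target.

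These arguments limit the likely size of the problem. They do not remove the conflict between the two sections, and an analysis plan should not have to override an eligibility rule written in the protocol.

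**Conclusion.** The point holds in conditional form. As written, the exclusion permits randomised patients to be removed because they died, and it contradicts the definition of non-survivors under Clinical Data. That contradiction arises for every patient randomised within 24 hours of ICU admission who dies inside that window.

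The numerical effect cannot be derived from the document. With 30 per arm and a true mortality of 30% or 40% in both arms, the scenarios tabulated run from -7.8 to +5.4 points. They rest on assumed mortality, assumed early deaths and equal allocation. They show only that a handful of removals matters in a trial of this size. The text needs amending on either reading of the timing: if randomisation is early, the rule is unsound; if it is late, the protocol has to say so.

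**What to change.** Choose one of two amendments.

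1. Delete the bullet, and state that every randomised patient, including those who die early, is counted in the mortality analysis from randomisation. This agrees with the Clinical Data definition.
2. If the intended population is patients who have survived 24 hours in the ICU, state that eligibility is confirmed and randomisation done only after that time, so that the criterion is applied before allocation. The mortality result then describes 24-hour survivors and should be labelled so.

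The first costs about one line, and a few early deaths stay in the analysis and add noise. The second also needs little text, but it changes when patients enter the trial and which patients the result describes.

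How early deaths enter the vasopressor and SOFA analyses is a separate choice. Giving them a worst rank, for example, would not fit the unpaired t-tests on means in the Statistical Analysis section and would need its own justification. It should not be folded into this amendment.

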### Statistical Analysis and Sample Size:

- Data entry, processing, and statistical analysis will be carried out using SPSS v29. Frequency tables with percentages will be used for categorical variables and descriptive statistics (mean  $\pm$  standard deviation or median with interquartile range) will be used for numerical variables. Tests of significance (Chi-square, student's t-test, or Mann Whitney's test) will be used according to the normality of the data. A P-value of less than 0.05 will be considered statistically significant. Total sample size 52 cases (organ dysfunction using SOFA score will be used as a primary outcome with proposed large effect size (0.8) and  $\alpha=0.05$  and power=0.80, so, 26 cases are needed in each group).

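### Vasopressor use at entry, a likely strong predictor of the primary outcome, is used in neither the described allocation nor the stated unadjusted test; adjusting for it would gain precision

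*Protocol*

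**What the plan says.** All references are to the protocol; no statistical analysis plan is at hand.

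- **Primary outcome.** After the description of Group 2, the primary outcome is given as "vasopressor dose".
- **Entry.** Study Population plans 60 patients. It accepts severe sepsis on any one of a list that includes hypotension but also raised lactate, bilirubin, creatinine, low platelets or coagulopathy. Hypotension is not required.
- **Vasopressor use.** The conventional therapy described for Group 1 starts a vasopressor when adequate fluid has not restored haemodynamics.
- **Allocation.** The paragraph after the exclusion list says: "Randomization will be performed using computer-generated random number tables in opaque sealed envelopes", prepared by an anaesthesiologist outside the study. It adds: "Patients will be randomly divided into two groups using a computer-generated random number chart". No stratification factor is named.
- **Analysis.** Statistical Analysis and Sample Size lists chi-square, Student's t and Mann-Whitney tests, chosen by normality. Statistical Analysis names an unpaired t-test for numerical data between groups. Neither section uses a baseline covariate.

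**The concern.** A patient already on a vasopressor at randomisation contributes a dose from the start. A patient who entered on platelets or bilirubin alone may never have one. Entry status is therefore likely to explain a good part of the patient-to-patient variation in the primary outcome, and the protocol as written makes no use of it.

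Two things are at stake. First, in a trial of this size the arms may by chance differ noticeably in the share already on a vasopressor, and an unadjusted result would then be hard to interpret. Second, variation that the test could remove stays in the error term, so power for the primary outcome is lower than it need be with the same patients.

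**Working it through.** **1. The plan's own figure, and whether arm size matters.** For effect size 0.8, two-sided alpha 0.05 and power 0.80, the exact two-sample t calculation gives 25.52, so 26 per group, with power 0.807. The figure of 26 reproduces. Under simple 1:1 randomisation the arm size is Binomial(N, 0.5):

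| N | P(exactly equal arms) | Power, equal arms | Mean power, simple randomisation |
|---|---|---|---|
| 52 | 11.0% | 0.807 | 0.800 |
| 60 | 10.3% | 0.861 | 0.855 |

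Unequal arms cost less than one percentage point of power on average, so arm size is not the issue.

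**2. Chance imbalance in vasopressor use at entry.** Inputs: N = 60 (Study Population); simple randomisation (assumed, since the protocol names no restriction); share on a vasopressor at entry p = 30%, 50% or 70% (assumed, since the protocol gives none).

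Normal approximation with 30 per arm: SD of the difference = √[p(1−p)(1/30 + 1/30)].
- p = 0.5: √(0.25 × 0.0667) = 0.129, so 20 points is 0.20/0.129 = 1.55 SD.
- p = 0.3 or 0.7: √(0.21 × 0.0667) = 0.118, so 20 points is 0.20/0.118 = 1.69 SD.

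Exact calculation: with K of 60 on a vasopressor, arm 1 receives a ~ Binomial(K, 0.5) of them and b ~ Binomial(60−K, 0.5) of the others. Sum the probabilities where the two proportions differ by at least the threshold.

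| On vasopressor | Gap ≥ 10 points | Gap ≥ 20 points |
|---|---|---|
| 18 or 42 of 60 | 42% | 10.0% |
| 30 of 60 | 52% | 15.5% |
| 50% expected, count varying | 45.5% | 13.0% |

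The expected difference is zero in every row.

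**3. What adjustment is worth.** Let patients on a vasopressor at entry have a mean outcome d within-status SDs higher than the rest. Entry status then explains R² = p(1−p)d² / [1 + p(1−p)d²] of the outcome variance. The unadjusted variance exceeds the adjusted one by the factor 1 + p(1−p)d². At p = 0.5:
- d = 1: factor 1 + 0.25 × 1 = 1.25 (R² = 0.25/1.25 = 0.20).
- d = 1.5: factor 1 + 0.25 × 2.25 = 1.56 (R² = 0.5625/1.5625 = 0.36).
- d = 2: factor 1 + 0.25 × 4 = 2.00 (R² = 0.50).

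The protocol gives no value for d, so these show a range only.

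**4. Illustrative simulations** (60 patients, 50% on a vasopressor at entry, a 40% dose reduction; all assumed). In one, power rose from about 33% unadjusted to 48% with entry status in the model. In another, which also assumed a lognormal dose and 20% of the remaining patients starting later, it rose from about 40% to about 60%; stratified allocation plus adjustment gave about 62%. The levels depend on the assumed dose distribution; the direction does not change.

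With no drug effect, the unadjusted test after simple randomisation had a type I error of about 4.5% to 5%. Among trials with a gap of 20 points or more it was about 17%, falling to about 5% with adjustment. Stratifying the list but keeping the unadjusted test gave about 1%, which is conservative.

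**The case against.** The strongest reply is that unstratified randomisation with an unadjusted test is valid. Chance imbalance is already in the test's standard error, and randomisation balances vasopressor use in expectation. This stands. A reader might infer that the scheme leaves the arms unbalanced or biases the primary comparison; the documents support neither, and the overall type I error in step 4 is nominal.

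A reader might also infer that allocation is certainly simple randomisation. The protocol does not say so. A computer-generated list can be blocked or stratified, block details are often withheld to protect concealment, and numbering of envelopes is the same kind of unstated detail. None of these silences is a defect on its own.

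A third tempting reading is that the trial will miss the stated "26 cases are needed in each group". Step 1 shows that this hardly matters, and that figure was sized on the SOFA score, so it says nothing about adequacy for vasopressor dose.

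Finally, the share on a vasopressor at entry is unknown. The exclusions for late septic shock with multiple organ failure and for APACHE II above 25 may lower it, and the protocol does not say whether randomisation precedes the start of a vasopressor. If few patients have a running dose at randomisation, the gain from adjustment shrinks.

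What survives is narrower: the protocol positively states an unadjusted test for an outcome that entry status probably predicts strongly.

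**Conclusion.** The point holds as a loss of precision, not as bias. Vasopressor status at entry is left to chance in the design as described and ignored in the analysis as stated. Under simple randomisation of 60 patients with 30% to 70% on a vasopressor, a gap of 20 points or more arises in about 10% to 16% of trials. Adjustment protects the interpretation of such a trial and, under the illustrative assumptions, adds roughly 15 to 20 percentage points of power. Nearly all of that comes from the covariate; stratified allocation adds little.

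The conclusion rests on three assumptions that the protocol does not settle: the list is unrestricted, a substantial minority or more of patients are on a vasopressor at randomisation, and entry status predicts later dose well. Severity is minor to moderate.

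**What to change.** **Main change.** Name vasopressor use at randomisation (yes/no, or dose) as a covariate in the primary comparison, and replace the unadjusted t-test with a linear model or ANCOVA. If the dose data call for a rank method, a rank test stratified by entry status does the same job. Record the status before the envelope is opened, so that the covariate cannot be affected by allocation. The cost is one pre-specified line of analysis and one data item. The planned vasopressor records and day-1 SOFA should already supply it, provided the value used predates randomisation. If enrolment has begun, this can still be fixed before any comparison by group.

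**Optional, only if enrolment has not begun.** Have the same independent anaesthesiologist prepare separate lists for patients on and not on a vasopressor, with varying block sizes. Avoid blocks of 2: no placebo is described, so past allocations may be known and the second assignment in such a block predictable. Keep the stratum in the analysis, because an unadjusted test after stratification is conservative. The cost is a new list and new envelopes.

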## Procedures:

### Clinical Evaluation:

- History and physical examination with special emphasis on vital signs (Blood pressure, pulse, Temperature, Respiratory Rate) and Glasgow Coma Scale to be continuously evaluated. drug to interaction will be considered when addi new drugs like the amino acids L-dopa and L-tryptophan, anorexiant, anticonvulsants, antidepressants, anxiolytics, calcium channel blockers, cyproheptadine, lithium salts, and drugs of abuse.
- Basl line ECG and calculation of QR interval and detection of ant type of arrythemia by cardiologist then follow up every otherday
- 10 ml blood sample will be taken there will be no leftovers and no sample storage after research ends and the following labartory parameters will be measursed

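### The scheduled ECGs and barred drugs carry no written rule for holding fluoxetine, so its 28-day course has no stated exit for safety

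*Protocol*

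**What the plan says.** - **Dosing.** The Group 2 paragraph adds fluoxetine 40 mg to conventional sepsis therapy, "daily for 28 days or until discharge from the ICU or death". No other end of dosing is given.
- **Entry, cardiac.** The Exclusion Criteria bar "patients with prolonged QT interval or premature ventricular beats", without a millisecond cut-off.
- **Entry, drugs.** The same list bars "Concurrent use of MAO inhibitors or linezolid or any drugs increase QR interval like flecainide".
- **Monitoring.** Clinical Evaluation, under Procedures, calls for "Basl line ECG and calculation of QR interval and detection of ant type of arrythemia by cardiologist then follow up every otherday".
- **New drugs on treatment.** The same section says that "drug to interaction will be considered when addi new drugs". It then gives an open list of examples, which does not name linezolid.
- **Blinding.** Study Design, under Methods, calls the trial double-blind. Group 1 is described as conventional therapy alone, and no placebo is mentioned.

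**The concern.** The Protocol itself identifies the hazard. It keeps out patients with a prolonged QT or ventricular ectopy, keeps out certain drugs, and pays for serial ECGs read by a cardiologist. It then stops short of saying what happens when an ECG is abnormal or when a barred drug becomes necessary.

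What is at stake is patient safety first and consistency second. Whether fluoxetine is held rests on individual judgement, so two patients with the same ECG may be treated differently. Nothing asks for the date or reason of a stop, so such differences could not be reconstructed afterwards. If blinding works as claimed, the clinician who sees the abnormal ECG may not know whether the patient is on fluoxetine, and unaided judgement is then a weak substitute for a rule.

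**Working it through.** The Protocol has no figure to reproduce on this point. The check sets its texts side by side and then counts who is covered.

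**1. Ends of dosing against the entry bars.** The Group 2 paragraph gives three ends: day 28, ICU discharge and death. Two exclusion lines describe states that could also arise during treatment: the QT and ventricular-beat line, and the concurrent-drug line. Neither is among the three ends (0 of 2).

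**2. Monitoring against action.** Clinical Evaluation supplies a test, a reader and a frequency. It supplies no limit and no consequence. If the baseline ECG falls on day 1 (an assumption), every-other-day follow-up runs on days 3, 5, …, 27, which is (27 − 1)/2 = 13 follow-up ECGs over a full course. None of them has a written consequence for dosing. The daily liver, kidney and coagulation tests under Routine Laboratory Investigations are not tied to dosing either.

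**3. Name of the interval.** The cardiac exclusion says QT. The drug exclusion and the ECG line both say QR. No QT or QTc limit in milliseconds appears anywhere in the text shown.

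**4. Could a barred drug be needed after randomisation?** The hospital protocol summarised under Group 1 calls for broad-spectrum anti-infectives chosen by site of infection and local antibiogram. Microbiological Studies takes cultures on day 1. A need for linezolid after fluoxetine has started is therefore foreseeable, although its frequency is not given. The only on-treatment instruction is that interactions are to be considered. It does not say whether fluoxetine is held or the new drug avoided.

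**5. Patients covered.** The Protocol gives three totals:
- Study Population, "ASA II, III 60 patients": 60/2 = 30 in the fluoxetine group, if the split is equal (an assumption).
- Statistical Analysis and Sample Size: 52/2 = 26.
- Sample Size Calculation: 46/2 = 23.

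These are the numbers to whom the dosing instruction applies. They are not numbers expected to be harmed or to meet a hold criterion.

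**6. Search for a rule elsewhere.** No section shown contains a hold, stop, dose-reduction or withdrawal rule. Title, signature, contact and consent pages were removed, so the absence is established for the visible text only.

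**The case against.** The strongest reply is that the Group 2 paragraph states a planned duration and nothing more. Clinicians may always stop a drug, a cardiologist reads the ECGs, vital signs are followed continuously, and interactions are to be considered. On this view surveillance and freedom to stop are both present, and only a numeric trigger and an explicit action are missing. That is correct, and it sets the limit of the point. A reader might infer that the Protocol orders fluoxetine to continue through a prolonged QT. It does not: it is silent, and silence is not an instruction.

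A reader might also infer that naming the interval QR would lead to the wrong measurement. The documents do not support that. The section has several typing slips, the exclusion list writes QT correctly in one line, and a cardiologist is named in the ECG instruction. It is very probably a slip, to be corrected as such.

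On drugs, the word for concurrent use may be meant to run through treatment, and the open list of interactions may be meant to cover linezolid and MAO inhibitors. Even on that reading, nothing says whether fluoxetine is held when one of them must be started. This part stands, but it is weaker than the ECG part.

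The argument could be stretched to the exclusions for "History of allergy to fluoxetine" and "History of seizures". Both concern the patient's past, and they add little to the case.

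Finally, an unseen SAP does not answer the point. When to hold a drug is a rule of clinical conduct and belongs in the Protocol.

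**Conclusion.** The point holds in a limited form. The Protocol schedules safety ECGs without a threshold or an action, and bars certain drugs without saying what to do if one is needed later. Dosing as written therefore has no stated exit for the events its own exclusions treat as disqualifying. The gap covers the whole fluoxetine group (23, 26 or 30 patients, as derived above). The number who would reach a hold criterion cannot be derived, and no effect on power or on the primary comparison is claimed.

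The conclusion assumes that no rule sits in the removed pages. The argument from blinding also assumes that the trial is run double-blind as stated. The amendment should be made as a cheap safety improvement; the gap does not invalidate the design.

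**What to change.** Amend the Group 2 paragraph so that study treatment is held:

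1. when a scheduled ECG shows QTc above one numeric limit, set by the trial cardiologist and written into the Protocol;
2. when the cardiologist confirms a new ventricular arrhythmia;
3. before linezolid, an MAO inhibitor or a QT-prolonging drug barred by the Exclusion Criteria is started.

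Make the rule workable under the claimed blinding. Either word it for study treatment in both groups, which requires that Group 1 receives a matching treatment, or name an unblinded person who applies it.

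Correct QR to QT in the Exclusion Criteria and in Clinical Evaluation. Record the date and reason of each hold. Keep these patients in the follow-up under Clinical Data and in the SOFA scoring, and analyse them in their randomised group.

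**Cost.** This is a short amendment that uses ECGs and cardiologist readings already scheduled. The new decisions are the QTc limit and how the rule operates under blinding. The downside is some loss of fluoxetine exposure, which could be larger if many interval-prolonging drugs are used. The Protocol does not allow its size to be estimated.
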